### Sample size, recruitment and randomization

We estimated sample size on the basis of aiming to show an improvement of 2,500 steps/d (and a baseline value of 7,500 steps/d) with an approximate standard deviation of ±3,000 steps/d (as established through recently published papers and systematic reviews of pedometer-based interventions conducted from 1966–2007 [30-32], as well as using the outcomes from recent pedometer studies conducted in RSA [20,25]). A sample size of 30 participants per arm of the study is required to ensure 80% statistical power and with a p-value set at <0.05. However, if a modest improvement of 1 500 steps/d is considered, a sample size of approximately 85 participants per arm is required. Considering this possibility and the likelihood of performing sub-group analyses of the data based on factors such as age and gender, a sample size of 150 participants in the INT and CTL respectively would be an appropriate estimate to account for these factors.

In order to achieve this, 1200 employees attending wellness events will be targeted. Of these, a minimum of 480 employees (40%) will be identified to be in the contemplation stage of TTM [33]. On an assumption that at least eighty percent (N=385) will agree to participate (as in the contemplation stage of TTM for PA), of which approximately 90% (N=345) will complete a 3 day blinded pedometer wear [34], 175 participants will be randomly assigned to the INT and wait-listed CTL respectively. An expected 15-20% loss to follow-up [5,35] will result in a final number of approximately 150 per arm of the study for analyses.

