### Inclusion and exclusion criteria

Employees attending the wellness event and willing to be included in the study will be eligible to participate. Other inclusion criteria include: being between the age of 21 years (inclusive) and 50 years (exclusive); being identified as in the contemplation stage of TTM towards improved PA and having a contract with employer until end of the 12-week measurement period so that completion of the intervention is possible. Employees will be excluded for the following reasons: pregnancy; diagnosis or treatment of cancer; any other condition that makes PA difficult/impossible; contract workers whose employ with the company will end before the follow up measurement at week 12; non-compliance of a minimum 3 day (including 1 weekend day) blinded pedometer wear.

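### At the plan's own 15-20% loss to follow-up, about 138-147 participants per arm are analysed; the 20% end falls 7-8% short of the stated 150 or so

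*Protocol article*

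**What the plan says.** All the figures stand in the protocol article under Sample size, recruitment and randomization. The authors settle on 150 per arm as a suitable size, to cover a modest improvement of 1,500 steps/d (for which they state about 85 per arm) and likely subgroup analyses by factors such as age and gender. They then describe how recruitment is to reach it:

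- The starting point is 1,200 employees at wellness events.
- The first step is readiness for change: "a minimum of 480 employees (40%) will be identified to be in the contemplation stage of TTM".
- Agreement is put at 80% or more of these, given as 385 people.
- The baseline step follows: "approximately 90% (N=345) will complete a 3 day blinded pedometer wear".
- Randomisation is then set at 175 per arm.
- The section ends with attrition: "An expected 15-20% loss to follow-up [5,35] will result in a final number of approximately 150 per arm of the study for analyses".

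The Inclusion and exclusion criteria section adds conditions that are not steps in this chain: age from 21 to under 50, an employment contract running to week 12, and exclusion for pregnancy, cancer or any other condition that makes physical activity difficult or impossible. It also requires a weekend day within the minimum baseline wear.

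**The concern.** The last two links of the chain do not fit together across the stated range. To finish with 150 of 175, the loss must be 14.3%, which lies just below the range of 15-20%. The upper end of the range leaves clearly fewer than 150. The number randomised is also slightly above the number that the chain supplies (350 against 345), so the two roundings push the same way.

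The eligibility criteria matter to the same figure. If some of the employees in the contemplation stage are too old, on short contracts or excluded for health reasons, the numbers fall further unless the 40% and 80% rates already allow for this. The article does not say whether they do.

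At stake is the analysed size the article states. It is also the size offered as allowing for subgroup analyses, so any shortfall is felt there first.

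**Working it through.** **Inputs, all from the sample size section:** 1,200 employees targeted; 40% in the contemplation stage; 80% agree; 90% complete baseline wear; 175 randomised per arm; 15-20% lost; target 150 per arm; SD 3,000 steps/d; modest difference 1,500 steps/d; significance level 0.05. Sidedness is not stated, and two-sided is assumed here.

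**1. The recruitment chain reproduces.**
- 1,200 × 0.40 = 480
- 480 × 0.80 = 384 (stated 385)
- 384 × 0.90 = 345.6 (stated 345)
- 345 / 2 = 172.5 per arm, against 175 stated. 2 × 175 = 350, and (350 − 345) / 350 = 1.4%.

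**2. Analysed size = randomised per arm × (1 − loss).**

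| Randomised per arm | 15% loss | 20% loss |
|---|---|---|
| 175 (as stated) | 148.75 (0.8% below 150) | 140.0 (6.7% below) |
| 172.5 (from 345) | 146.6 (2.3% below) | 138.0 (8.0% below) |

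The loss that leaves exactly 150 is 1 − 150/175 = 14.3%.

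**3. What 150 analysed would need.**
- At 15% loss: 150 / 0.85 = 176.5, so 177 per arm, 354 in total.
- At 20% loss: 150 / 0.80 = 187.5, so 188 per arm, 376 in total.
- Overall yield of the chain: 0.40 × 0.80 × 0.90 = 0.288. Employees to target: 354 / 0.288 ≈ 1,230 and 376 / 0.288 ≈ 1,306, against 1,200 planned.

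**4. Effect on power for 1,500 steps/d.** Normal approximation: power = Φ(δ / (SD·√(2/n)) − 1.96), with δ/SD = 1,500/3,000 = 0.5.
- n = 150: 0.5 × √75 = 4.330; Φ(2.370) = 99.1%
- n = 138: 0.5 × √69 = 4.153; Φ(2.193) = 98.6%
- Half-sample subgroup, n = 75: 0.5 × √37.5 = 3.062; Φ(1.102) = 86.5%
- Half-sample subgroup, n = 69: 0.5 × √34.5 = 2.937; Φ(0.977) = 83.6%

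**5. Detectable difference at 80% power.** Normal approximation: (1.960 + 0.842) × 3,000 × √(2/n), which gives 970 steps/d at n = 150 and 1,012 at n = 138. The two-sample t-test gives 974 and 1,015.

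**The case against.** The strongest defence is that the section deals in round numbers and says so. The contemplation count is worded as a minimum, the agreement rate as at least 80%, and both the wear rate and the final number as approximate. On that footing:

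- A reader might infer that 345 people cannot fill 350 places. The gap is 1.4%, which is rounding. An overall yield of 350 / 1,200 = 29.2% instead of 28.8% would close it, and two of the three rates are given as floors. This part of the defence stands.
- A reader might infer that 345 is a ceiling, because the age, contract and health criteria take nothing off. The wording of the rates does not support that. The Study setting and study population section also makes the invitation to take part subject to the inclusion criteria, so ineligible employees may already be among those not counted as participants. What remains is that the article does not say how eligibility relates to the rates. It gives no figure for these exclusions, so none is put on them here.
- At 15% loss, 147 to 149 per arm is a fair reading of about 150. This stands too.
- The 150 is not a computed requirement. The article's own requirement for 1,500 steps/d is about 85 per arm, and 138 exceeds that by 62% (138/85 = 1.62). This limits the consequence, but it does not make the stated figure right.

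The defence does not reach the 20% end. The article gives that rate as part of its expected range, and 138 to 140 is not about 150.

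**Conclusion.** The point holds as a minor correction of a stated figure. Under the article's own assumptions the analysed size is 140-149 per arm from 175 randomised, or 138-147 from the 345 the chain supplies. The lower end is 7-8% below 150.

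A reader might go further and conclude that the trial is underpowered or that its subgroup analyses are no longer covered. The figures do not support this. At 138 per arm, power for 1,500 steps/d falls by about half a percentage point overall (99.1% to 98.6%). In a half-sample subgroup it falls by about three points (86.5% to 83.6%) and stays above 80%. These values rest on SD 3,000, a two-sided 0.05 level, equal arms, subgroups of half the sample and the loss rates as printed. They concern the difference between arms within one subgroup, not a test of interaction, and smaller subgroups would have less power.

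**What to change.** In the sample size section, give the expected numbers as about 345 completing baseline wear, about 172 randomised per arm, and about 138-147 analysed per arm at 20% to 15% loss. Quote the operating characteristics at the lower end: about 98.6% power for 1,500 steps/d with SD 3,000, a detectable difference of about 1,015 steps/d at 80% power, and about 84% power for 1,500 steps/d in a half-sample subgroup. Add one sentence saying whether the 40% and 80% rates already allow for the age, contract and health criteria.

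This costs wording only, and the stated final size becomes slightly less favourable. If 150 analysed per arm is to be kept as a firm target, the alternative is to plan for 177-188 randomised per arm. At the stated rates that means about 1,230-1,306 employees, or 30 to 106 more than planned. The power figures give no strong reason to go that far.

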### Inclusion and exclusion criteria

Employees attending the wellness event and willing to be included in the study will be eligible to participate. Other inclusion criteria include: being between the age of 21 years (inclusive) and 50 years (exclusive); being identified as in the contemplation stage of TTM towards improved PA and having a contract with employer until end of the 12-week measurement period so that completion of the intervention is possible. Employees will be excluded for the following reasons: pregnancy; diagnosis or treatment of cancer; any other condition that makes PA difficult/impossible; contract workers whose employ with the company will end before the follow up measurement at week 12; non-compliance of a minimum 3 day (including 1 weekend day) blinded pedometer wear.

### Ethical considerations and pre-participation screening

This study will be conducted in accordance with the Declaration of Helsinki, Good Clinical Practice as well as the ethical laws of SA. Ethical approval for the study was obtained from the Human Research Ethics Committee of the Faculty of Health Sciences, University of Cape Town (UCT), SA (reference number: 044/2009) and the study has been registered by the SA Department of Health (DOH-27-0112-3951). Following agreement to participate in the study, the Physical Activity Readiness Questionnaire (PAR-Q) [36] will be administered to ensure that there are no health risks to improving PA levels during and after the intervention. Employees who agree to participate in the study will be asked to sign an informed consent form prior to participating in the study. Participants will be assured that their participation in the study is voluntary and that they may withdraw at any time. They will also be reassured that their withdrawal will not have any negative impact on their employment, and that they will continue to receive all usual care health insurance benefits and/or programs. The participants will also be assured that their employer will not have access to any of the information collected for the research study, and that all information is strictly confidential.

### Testing protocol

All eligible employees who sign the informed consent will be required to wear a blinded pedometer (Omron HJ 720 ITC) for 7 days during week 1 and week 12 of the study. Upon return of the pedometer (after week 1), steps/d data will be electronically downloaded by the researcher according to the Omron Health Management Manager software protocol [37] and feedback (in terms of average total steps/d and information relating to moderate intensity steps (*“steps that count”*)) will be provided to each participant. Simple messages to improve PA levels will be discussed in keeping with the PA recommendation of 30 minutes of moderate PA (MPA) at least five times a week [38]. Participants will be encouraged to improve their PA levels steadily (for example by 10% per week until 30 minutes of MPA is achieved) during the subsequent 10 weeks. They will then be randomly allocated to an INT or wait-listed CTL and participants in the INT will be provided with an un-blinded pedometer for the subsequent 10 weeks. Those included in the INT will be guided as to how to download their pedometer data and its interpretation. (A 1-page step by step guideline will be provided and participants will be advised to contact the researcher for assistance, if need be). Participants will be advised to download data whenever suitable (This would provide the researcher with information as to how often the downloading feature was accessed).

Following the blinded pedometer wear at week 12 (INT and CTL), an HRA similar to the initial HRA will be conducted. The results obtained (HRA information and pedometer data) will then be compared with the information obtained in week 1 to establish the intervention effect. Participants in the CTL will be offered the pedometer intervention after the HRA conducted at 12 weeks.

Figure 1 provides a flow diagram of the randomized controlled trial intervention plan.

### Health Risk Appraisal (HRA)

Aspects of the HRA relevant to our study include demographic factors (i.e. age and gender), self-reported volume and intensity of PA, as well as information relating to intention and readiness for change toward improving PA. Additionally, BP, body height and body weight, %BF, BMI and waist circumference will be measured. The HRA will be conducted by qualified, trained staff and will form part of the wellness event conducted.

### Pedometer wear and data recording

Participants will be asked to wear the Omron HJ 750 ITC pedometer, attached to the left or right hip as conventionally worn in most studies [39], by both INT and CTL in weeks 1 and 12 respectively. After baseline measurement (week 1), only the INT will continue with subsequent un-blinded pedometer wear. Following the blinded pedometer wear, the pedometer data will be downloaded electronically by the researcher according to the Omron Health Management Manager Software protocol [37]. One of the unique features of the pedometer is the ability to provide an hourly representation of steps/d. Furthermore, in addition to indicating total steps/d, the output illustrates steps accumulated as being “aerobic” or “non-aerobic” according to the Omron classification that integrates both intensity and duration. A record of steps classified as “aerobic” (≥60steps/min, minimum duration of 1-minute) and “non-aerobic” (<60steps/min and/or <1-minute duration) is therefore provided. Similarly, total time spent accumulating “aerobic” steps in minutes/day (aerobic time) and the number (in hours) of sedentary time can be identified.

The validity and reliability of this brand and model of pedometers has been studied at various mounting positions under prescribed and self-paced walking conditions with both healthy and overweight adults and is suggested as an accurate measure of step counts [40,41].

### Intervention content

Pedometer data will be requested (via e-mail) from the INT at bi-weekly intervals. INT participants will be provided with individualized, emailed feedback and a general pamphlet on ways to increase PA following the bi-weekly receipt of pedometer data, via email. The CTL will similarly be provided with the general pamphlet (as in the INT) at bi-weekly intervals.

The individualized feedback (provided only to the INT) will include information on the average daily steps/d accumulated, the number of days (if any) that aerobic steps were accumulated, and the volume thereof in the form of a personalized email. The feedback will also include information such as the highest number of steps/d accumulated by the individual over the past two weeks and the category within which the average steps/d fall, as per current steps/day categorizations [22,23,42] (Figure 2). Participants will be encouraged to steadily increase their steps by approximately 10% per week until the target of at least 30 minutes of aerobic steps (displayed as “orange” steps on the pedometer download) is achieved and/or maintained by the end of the intervention.

**Figure 2 F2:**
[figure not shown]
Illustrated feedback characteristics.

The general supportive/motivational messages will include a key message (such as “be active everyday” or “walk tall”) and a few strategies to achieve this (for example, “Use the stairs instead of the lift/escalator”; “Walk fast enough so as to increase your breathing rate yet not feel out of breath”).

The purpose of the bi-weekly email is to provide a summation of pedometer-based PA patterns; to remind and reinforce current PA recommendations and to provide some strategies and/or options for “adding steps” to one’s day. Figure 2 and Figure 3 provide examples of a weekly email, respectively.

**Figure 3 F3:**
[figure not shown]
Illustrated general motivational messages.

### Outcome measures

The primary outcome measure (daily PA levels in terms of steps/d) will be assessed at baseline (week 1) and end (week 12) for both the INT and CTL, in order to detect changes in daily PA over time, as a function of the intervention. Data will be derived from the pedometer and expressed as steps/day. More importantly, information on the volume of sustained and moderate-vigorous intensity steps (“*Steps that count”)* will be assessed at baseline (week 1) and at the end of the intervention (week 12) for both the INT and the CTL. Secondary outcomes such as systolic BP and diastolic BP, BMI and %BF (as per clinical measures of HRA) will be assessed at week 1 and week 12 in both groups.

### Statistical analyses

Statistical analyses to determine effectiveness of the intervention will be based on group allocation, regardless of the actual intervention received or of adherence to the intervention, i.e. intention to treat analysis. Linear regression analyses will be performed with the follow-up value of the outcome measure as the dependent variable and adjustment for the baseline value. Assumptions of linear regression analysis will be verified with residual analysis. To assess whether the differences in the primary outcome between the groups are affected by random differences between them, an analysis of covariance (ANCOVA) will also be undertaken. For the process evaluation, descriptive analyses will be conducted among INT only. All analyses will be performed with STATISTICA version 8 (StataSoft Inc., Tulsa, OK, USA) and the significance level will be set at p-values <0.05.

## Discussion

The purpose of this paper is to outline the rationale behind, and the development of, an intervention aimed at improving the daily PA in a South African employed population, and to describe the study protocol evaluating its effect.

A recent literature review identified thirty studies using web-based interventions to increase weight loss and/or PA [43]. Twenty-eight of the studies (93%) reported positive changes in moderate to vigorous PA level, fruit and vegetable intake and psychological factors [43]. The review suggests that web-based interventions are a useful educational tool for increasing awareness and making healthy behavior changes. The self-maintained improvement of PA and maintenance thereof is a further aspect that can also be monitored and evaluated over regular time intervals.

There are limitations that must be noted in the study design. Firstly, there is an element of selection bias as the study will involve selection from a convenience sample of persons who are recruited as a result of attending a corporate HRA. Secondly, the general information provided to both the INT and CTL is the same irrespective of individual progress toward improved PA. Also, the CTL receives the same general motivational messages as the INT, bi-weekly, which may lead to increased PA in the CTL and a resultant weakened effect of the intervention. A further limitation is that the pedometer will be used as a measurement tool (albeit blinded for measurement at weeks 1 and 12, respectively) and during the 10 week intervention.

The study has strengths that can be noted. To our knowledge, this will be the first pedometer-based intervention conducted in SA (other than the pilot feasibility study conducted) and will provide useful information regarding potential for PA improvements through pedometry in an adult working group. This is the first pedometer-based intervention, to our knowledge, that takes into account intensity and duration of PA during free-living wear to provide information on patterns of PA in an employed, adult population. The study will, therefore be useful for further pedometer-based intervention initiatives that can be applied in other contexts and settings on a larger scale.

With a focus on daily PA using individualized, brief feedback and self-monitored, pedometer-measured PA, the success of such an intervention will have widespread public health implications, particularly if shown to produce successful outcomes in the limited extent of external support.
